### Secondary analysis

Secondary analysis includes investigating the effect of fibrinogen on:the total number of units of allogeneic products (red blood cells, FFP, cryoprecipitate and platelets) transfused within 24 h after study medication;the individual number of units of red blood cells, FFP, platelets and cryoprecipitate transfused after study medication within 24 h and until discharge;the total number of units of allogeneic products red blood cells, FFP, cryoprecipitate and platelets) plus 1 unit for every 250 ml cell salvage transfused within 24 h after study medication and until discharge,

and will be analysed using similar methods to those used in the primary analysis.

The effect of the intervention on the proportion of women receiving no allogeneic blood products, requiring cryoprecipitate or fibrinogen concentrate as subsequent therapy, and requiring invasive procedures, all within 24 h after the study medication and until discharge, will be examined by fitting logistic regression models again investigating for possible site-level clustering. The effect of fibrinogen on the incidence of exclusive breastfeeding will be explored using the same method.

Secondary outcomes also examined will be (1) the volume of cell-salvaged blood transfused within 24 h after the study medication and until discharge (2) and the measured abnormal blood loss within 24 h after study medication until discharge. These outcomes will be examined using linear regression models. Each of the regression model assumptions will be checked including but not limited to examining the distribution of the residuals and a plot of the residuals vs. predicted values. Similarly, Clauss fibrinogen and Fibtem parameters at 15 min and 24 h after the study medication will be examined between arms using a linear regression model adjusting for baseline measurements. The duration to (1) stopping breastfeeding or expressing breast milk and (2) any invasive procedure within 24 h after study medication and until discharge between arms will be examined using Cox’s proportional hazards model. Reasons for not exclusive breastfeeding will also be explored by using ordinal regression model.

The effects of fibrinogen concentrate infusion on the following safety endpoints will be examined: the proportion of women requiring high-dependency and intensive care admission and length of stay, the total length of hospital stay and the incidence of clinically diagnosed arterial and venous thromboembolism within 6 weeks of the study medication.

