## Methods and design

### Overview

This is a prospective, randomised, double-blind, placebo controlled trial. A total of 60 women will be included in the randomisation phase. The trial schema is shown in Figure 1.

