### Setting, location and follow-up

The study will recruit from four centres in the UK. The criteria for selection are based on size of the centres (a minimum of approximately 5500 deliveries per year) and an interest in peripartum clinical studies. The study team at each centre will be based on delivery suite and consist of a lead obstetrician, obstetric anaesthetist and midwife. All obstetricians, obstetric anaesthetists and midwifes at each centre will be involved in the study.

Women recruited to the observational phase, but who do not enter the interventional phase of the study, will be followed up until hospital discharge. Women participating in the interventional phase will be followed up until 6 weeks following randomisation or death. At 6 weeks post-delivery, women who entered the interventional phase of the study will be contacted by telephone. The telephone interview will obtain data on maternal hospital readmissions, incidence of venous or arterial thrombotic events, and initiation and duration of breastfeeding.

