### Outcomes and safety measures

The primary outcome is the total number of allogeneic blood products transfused after the study medication until discharge. The total number of allogeneic blood products transfused will be compared between the two arms. Secondary outcomes will be:the proportion of women receiving no allogeneic blood products until discharge and within 24 h after study medication,the number of units of red blood cells, FFP, platelets and cryoprecipitate transfused after study medication within 24 h and until discharge,the volume of cell salvaged blood transfused within 24 h after study medication and until discharge, the total number of units of red blood cells, FFP, platelets and cryoprecipitate transfused within 24 h after the study medication, the total number of units of red blood cells, FFP, platelets and cryoprecipitate plus 1 unit for every 250 ml cell salvage transfused within 24 h after study medication and until discharge, the measured abnormal blood loss within 24 h after study medication and until discharge, the proportion of women requiring cryoprecipitate or fibrinogen concentrate as subsequent therapy within 24 h after study medication and until discharge, the change in Clauss fibrinogen and Fibtem parameters before and 15 min and 24 h after the study medication, the proportion of women requiring invasive procedures (return to theatre, uterine brace sutures, uterine tamponade balloons, radiology intervention and hysterectomy) and the time of this intervention within 24 h after study medication and until discharge, incidence, duration and reasons for not exclusive breastfeeding.

The effects of fibrinogen concentrate infusion on the following safety endpoints will be explored: the proportion of women requiring high dependency and intensive care admission and length of stay, the total length of hospital stay and the incidence of clinically diagnosed arterial and venous thromboembolism within 6 weeks of study medication.

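### An ordinal regression model is named for the reasons for not exclusively breastfeeding, but no ordering of the reasons is stated, so any arm effect would depend on an arbitrary numbering

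*Protocol article*

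**What the plan says.** Outcomes and safety measures ends its list of secondary outcomes with "incidence, duration and reasons for not exclusive breastfeeding". Secondary analysis then gives each of the three parts its own model.

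- **Incidence.** After a sentence on logistic regression for other proportions, the article says "The effect of fibrinogen on the incidence of exclusive breastfeeding will be explored using the same method". This is logistic regression.
- **Duration.** "The duration to (1) stopping breastfeeding or expressing breast milk and (2) any invasive procedure within 24 h after study medication" is assigned to a Cox model.
- **Reasons.** "Reasons for not exclusive breastfeeding will also be explored by using ordinal regression model".

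The only account of how breastfeeding data are gathered is under Setting, location and follow-up: "The telephone interview will obtain data on maternal hospital readmissions, incidence of venous or arterial thrombotic events, and initiation and duration of breastfeeding". No section lists the reason categories or puts them in order.

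**The concern.** An ordinal model takes a response whose categories have a rank and, in its usual proportional-odds form, summarises an arm difference as one shift along that rank. Illness in the mother, separation from the baby, difficulty feeding or personal choice (my examples, not the article's) have no such rank. If numbers are assigned to them anyway, the shift is measured along an axis that the analyst has invented. A named secondary outcome could then carry an odds ratio and a p-value that reflect the coding rather than the treatment.

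There is a second, conditional issue. Only a woman who did not exclusively breastfeed has a reason for not doing so. That status arises after randomisation, and the article itself treats its incidence as something fibrinogen may affect. If the model is fitted only to those women, the two groups compared are no longer the randomised groups.

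**Working it through.** No figure in the article depends on this sentence, so there is none to reproduce. The check has two parts.

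**1. Could the ordinal model be meant for another outcome?** No. Incidence has logistic regression and duration has a Cox model, both in the same section. The ordinal model is left for the reasons alone.

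**2. Does the ordering matter to the result?** The article gives no data on reasons, so the counts below are assumed for illustration only.

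| Reason | A | B | C | D | Total |
|---|---|---|---|---|---|
| Arm 1 | 6 | 2 | 4 | 3 | 15 |
| Arm 2 | 2 | 6 | 3 | 4 | 15 |

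*Order-free test.* The column totals are 8, 8, 7 and 7, so the expected counts in each arm are 4, 4, 3.5 and 3.5.

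Chi-square = 2 × (2²/4) + 2 × (2²/4) + 2 × (0.5²/3.5) + 2 × (0.5²/3.5) = 2 + 2 + 0.143 + 0.143 = 4.29 on 3 degrees of freedom, p = 0.23. Renumbering the reasons leaves this unchanged.

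*Ordinal model.* A proportional-odds model (logit link, arm as the only covariate) was fitted under all 4! = 24 orderings. The odds ratio is that of a later category in arm 1 relative to arm 2.

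| Ordering | Odds ratio | p |
|---|---|---|
| A, C, D, B | 0.24 | 0.04 |
| A, B, C, D | 0.57 | 0.40 |
| D, A, B, C | 0.88 | 0.84 |
| C, B, A, D (the line above reversed) | 1.14 | 0.84 |
| B, D, C, A (the first line reversed) | 4.19 | 0.04 |

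*Number of distinct answers.* Reversing an ordering gives the same fit with the reciprocal odds ratio (1/0.24 ≈ 4.19), so k reasons yield at most k!/2 distinct fits: 24/2 = 12 for four reasons and 120/2 = 60 for five. With direction set aside, the 12 fits here span odds ratios from 1.14 to 4.19. One of the 12 falls below p = 0.05.

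**Size of the data.** "A total of 60 women will be included in the randomisation phase" caps the comparison at 60 women, 30 per arm. The number who would give a reason is not stated.

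**The case against.** Four points can be made for the plan.

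*The coding is not shown.* The category list and data form are not in the article, so a graded response cannot be ruled out. This stands. A reader might infer that the odds ratio must be meaningless. The article supports only the narrower statement that it names an ordinal model and states no order. It does not follow that the matter can be left to the full protocol, because the sentence fixes a model that does not suit the outcome as named.

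*The subgroup is not stated.* A reader might infer that the analysis is confined to women who did not exclusively breastfeed. That is the natural reading, but the sentence defines no analysis set. The statistical section on the interventional phase puts the secondary comparisons on an intention-to-treat, complete-case footing. A coding with exclusive breastfeeding as one level would keep every randomised woman with data. The subgroup point therefore holds only conditionally.

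*The instability can be overstated.* A reader might count 120 answers for five reasons, or treat 0.24 and 4.19 as two conflicting findings. They are one fit read from opposite ends. In the illustration every ordering that places A before B gives an odds ratio below 1, so much of the apparent reversal is labelling. The dependence of size and p-value on the ordering remains.

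*No arm effect is promised.* The sentence says only that reasons will be explored. However, it sits in a section on the effect of fibrinogen, next to sentences on between-arm comparisons, so an arm contrast is likely though not certain.

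**Conclusion.** The point holds in this form: an ordinal model is assigned to an outcome that is unordered as named, with no ordering stated, so an arm effect from it would depend on an arbitrary numbering. The illustration shows that the dependence can be material (p from 0.04 to 0.84 on identical data), but its counts are assumed and say nothing about what this trial would find.

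The conclusion rests on two assumptions: that the reasons are recorded as ordinary unranked categories, and that the ordinal model is meant to compare arms. The loss of randomised comparison follows only if the model is restricted to women who did not exclusively breastfeed.

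The consequence is small. This is the last item in the list of secondary outcomes and is described as exploratory. It affects neither the primary analysis nor the sample size. The correction is worthwhile but not urgent.

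**What to change.** Replace the sentence with a descriptive table of reasons by arm, giving counts and percentages of all randomised women with 6-week data (assuming reasons are gathered at the 6-week contact). That denominator keeps the randomised groups intact.

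If a test is wanted, use an unordered method: an exact test, or a multinomial logit if numbers allow. Keep exclusive breastfeeding as one of the categories so that all randomised women with data are included. The same test among reason-givers alone would bring back the subgroup problem. With at most 30 women per arm spread over several reasons, description may be all that the data support. A test that includes the exclusive-breastfeeding category also responds to a difference in incidence, which already has its own logistic model, and the report should say so.

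If a genuinely ordered scale exists, the ordinal model can stay, provided the scale, its order and the analysis set are written down before unblinding.

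The cost is one line in the analysis plan, with no new data and no change to the sample size.

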### Consent

All women at each study centre will receive an information leaflet in the antenatal period describing the study and consent process. Women will have the opportunity to indicate they would not wish to participate in the study at this stage. Consent will be obtained prior to birth for women planning an elective caesarean section or considered by a clinician to be at high risk of PPH, and immediately prior to study entry for other women. All women who give consent during a PPH, or consent is given on their behalf by a representative, will be seen by a member of the study team within 24 h of enrolment, or as soon as the woman’s condition permits, to discuss their participation in the study and obtain consent for use of the collected data.

### Research governance/ethical considerations

Full ethical approval for this study has been obtained from the Research Ethics Committee for Scotland (Ref: 13/SS/0008). The study will be conducted in compliance with the following:Declaration of Helsinki (Seoul, 2008)ICH Harmonised Tripartite Guideline for Good Clinical Practice.The Medicines for Human Use (Clinical Trials) Regulations 2004 (Statutory Instrument 2004 No. 1031) as amended by the Medicines for Human Use (Clinical Trials) Amended Regulations 2006 (Statutory Instrument 2006 Nos. 1928 and 2984) and Amended Regulations 2008 (Statutory Instrument 2008 No. 941).Research Governance Framework for Health and Social Care (Welsh Assembly Government 2nd Edition, September 2009, and Department of Health 2nd Edition, July 2005).

Two external bodies, a Data Monitoring and a Trial Steering committee will monitor the study progress.

## Discussion

Postpartum haemorrhage is a major cause of maternal morbidity and mortality. Fibrinogen appears to be a useful biomarker to predict the progression from moderate to massive PPH and the need for blood transfusion; however, it is not known whether replacement of fibrinogen to levels normal for the peripartum period (4–6 g/l), during an on-going PPH, would reduce bleeding and the need for transfusion. Although fibrinogen concentrate is not licensed for use in obstetric haemorrhage in the UK, it has been used off-label to correct hypofibrinogenaemia [17] and is the recommended treatment in other countries [25].

This trial is designed to detect haemostatic impairment rapidly and early during major PPH, identified by a near patient Fibtem A5 test below 16 mm, and replace fibrinogen to a level within the lower end of the normal range associated with delivery. Laboratory tests of fibrinogen take about 60 min to become available, and this is usually too slow to inform clinical intervention. The Fibtem A5 result is available within about 10–15 min of venesection and so can be used for decisions on therapeutic intervention. The decision to use the criteria of on-going bleeding and a low for delivery Fibtem A5, rather than a more pragmatic approach of randomising all women with a specific estimate blood loss, was made to minimise the chance of women being exposed to unnecessary IMP because many women in that situation would have a fibrinogen level above 4 g/l and therefore be unlikely to respond to a higher level The amount of fibrinogen concentrate or placebo given to all participants allocated to the intervention group will be based on the woman’s ideal weight for height and the Fibtem level. The dose will be rounded to the nearest whole number of grams of fibrinogen and the maximum dose of fibrinogen concentrate or placebo will be 8 g. The dose of fibrinogen is designed to increase the Fibtem A5 and Clauss fibrinogen to the lower end of the normal range for delivery. This level has been shown to be associated with a reduced requirement for blood products. This approach was preferred to the pragmatic approach of giving a standard dose of fibrinogen because this would be likely to be associated with both under- and over-dosing. The lower end of the normal range has been targeted to minimise the risk of thrombosis.

The study is designed to be blinded until the decision to give the first 4 units of FFP has been taken and hence the Fibtem A5 taken 15 min after IMP is not known to the clinicians managing the case. The primary endpoint is a comparison of allogeneic products between the two arms and knowledge of whether fibrinogen or placebo had been given is likely to affect the decision to give FFP, cryoprecipitate and fibrinogen. After the first FFP has been given and if the bleeding is on-going, clinicians need to know the fibrinogen level to optimally manage the case. At this point Fibtem A5 and Clauss fibrinogen tests can be performed that are available to clinicians. This will have the effect of partially unblinding the study because clinicians will know whether the Fibtem has increased or not. This partial unblinding was deliberately included in the study for women with on-going bleeding for safety reasons.

The primary objective is to investigate whether infusion of fibrinogen, based on a Fibtem A5 test, during a moderately severe PPH reduces the total number of allogeneic blood products (FFP, red blood cells, platelet concentrates and cryoprecipitate) transfused after study medication until discharge compared to placebo. This was chosen because the alternative primary endpoint of estimated blood is very difficult to measure accurately and reproducibly, especially in a multicentre study.

At the time of a PPH women may not have full capacity to give informed consent because of factors such as pain, altered levels of consciousness due to drugs and blood loss and anxiety. In addition, some clinical situations are so acute that there will be insufficient time to read and understand a full patient information sheet. The consent procedures adopted in this trial are based on recommendations of the Royal College of Obstetricians and Gynaecologists for obtaining consent to research in labour, which recommend against taking antenatal consent from all women if the likelihood of the event is less than one in ten deliveries [26].

## Trial status

The trial was initiated in June 2013. By November 2013, all four centres were screening and recruiting participants. By March 2014, 16 participants had been included in the randomisation phase.

## Abbreviations

APTT: Activated partial thromboplastin
AVC: Area under the curve
FBC: Full blood count
FFP: Fresh frozen plasma
ICH: International Conference of Harmonisation
IQR: Interquartile range
ITT: Intention to treat
MCF: Maximum clot firmness
NPV: Negative predictive value
PPH: Postpartum haemorrhage
PPV: Positive predictive value
RBC: Red blood cells
RCOG: Royal College of Obstetricians and Gynaecologists
ROC: Receiver operator characteristic curve
